**Fig. 2 Fig2:**
[figure not shown]
Participant sampling strategy. *Note.* Participant sampling by team, CWS caseworker, and condition. In total, 320 assessments will be collected from project participants from two County regions—8 team members from 8 child-family teams (4 per region) will participate in data collection following each of 5 CFT meetings. Half will be assigned to the control, CFT as usual, and the other half will be assigned to the intervention, CFT + AAR. Sampling is mirrored for Region 2

### Setting and context

The CWS system under study operates across six County regions. In the 2019/2020 fiscal year, 4080 children ages 6–17 were referred to CWS per month, with an average of 1488 open cases each month, and an average of 1026 children 6–17 years in out-of-home each month. Compared to the 2020 child population of County (*n* = 760,789), a greater percentage of children in out-of-home care were Hispanic/Latinx (50% vs 42%) and Black (18% vs. 5%). A lesser percentage of CWS children were White (26% vs 37%), and Asian/Pacific Islander (3% vs. 11%). Majority of CWS referrals are for general neglect (42%), emotional abuse (33%), physical abuse (31%), at risk/sibling abused (21%), and sexual abuse (18%) [56]. CWS caseworkers are typically female (83%) and Hispanic/Latinx (44%).

### Participants

There are four types of participants in this study. Participants will be (1) County CWS system leaders and caseworkers, (2) CFT informal and formal meeting members, (3) parents/caregivers with open CWS cases, and (4) children aged 6–17 with open CWS case. CWS caseworkers and CFT informal and formal support persons will be ≥ 18 years of age. Children and family members urrently open to CWS have a minimum age eligibility of 6 years to correspond with the CWS protocol for screening for behavioral health services need, and no maximum age limit for eligibility. Participants will be recruited from select regions, which will be determined in collaboration with CWS leadership prior to project implementation. Inclusion criteria for all groups of participants are intentionally broad to ensure valid analyses.

The research team will partner with County CWS to identify appropriate and representative CWS caseworkers to follow over the course of 5 CFT meetings. The 5 CFT meetings per CWS caseworker will be identified to best represent County CWS open cases. Additionally, only CFTs which include a child with an identified behavioral health services need will be included to optimize assessment of behavioral health services linkage. Behavioral health service need is determined by a preliminary administration of the Child & Adolescent Needs and Strengths (CANS) assessment by the CWS caseworker at the initial family visit. The CANS behavioral and emotional needs domain is employed for all children aged 6–17 as the screener for behavioral health services.

For children aged 6–17 open to CWS and with mental health services needs (identified via CANS screening and confirmed during initial CFT meeting perusual CWS), County Behavioral Health administrative data will be extracted to determine mental health service linkage. While children aged 6–17 may also participate in the CFT meeting, this is considered part of usual CWS services. No additional study participation from these children will be solicited. The proposed study will not apply any gender or minority exclusion criteria for participant selection. All efforts will be made to ensure that women and minority representation will be representative of County CWS.

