## Method

This study is part of a National Institute of Mental Health Advanced Laboratories for Accelerating the Reach and Impact of Treatments for Youth and Adults with Mental Illness Center [Center is P50 MH126231-01A1] that will implement a randomized control trial to develop and test team-based implementation strategies to improve services for children with mental health and developmental needs across service systems. This study aims to leverage and apply knowledge from team effectiveness research to improve outcomes associated with the services intervention currently used in CWS CFTs. Guided by the Exploration, Preparation, Implementation, Sustainment (EPIS) framework [49] and the Center’s Team Effectiveness for Implementation Science model (Fig. 1), this study aims to adapt and apply the team development intervention of the AAR to the implementation of the CFT meeting for a large, publicly funded, CWS system. Using a parallel group trial design, with non-equivalent comparison groups, and qualitative and quantitative methodology, this study will tailor and assess the impact of the AAR on enhancing CFT outcomes.

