#### Specific aim 3—interventions and comparisons

Consistent with the EPIS Implementation phase, the research team will pilot-test the AAR implementation strategy on improving CFT outcomes and explore team mechanisms. Specifically, to test the effectiveness of the AAR on improving outcomes associated with the CFT services intervention, we will implement randomization with parallel assignment in two CWS system regions, at the caseworker level. In each region, four CWS caseworkers will be followed as they engage in 5 CFT meetings (8 CWS caseworkers total). Within each region, two of the CWS caseworkers will be assigned to the team-enhanced implementation strategy, CFT + AAR (4 CWS caseworkers total), and two CWS caseworkers will be assigned to the standard implementation, CFT as usual (4 CWS caseworkers total). CFT as usual consists of CFT Meeting Facilitation wherein a mental health services organization partners with CWS to schedule the CFT meetings. The research team will utilize blocked randomization of CWS caseworker to intervention condition (CFT + AAR or CFT as usual) to ensure equal group sizes. As such, assignment of condition will be implemented by the research team without concealment or blinding.

Child mental health concerns are identified by a preliminary administration of the Child & Adolescent Needs & Strengths (CANS) [55] assessment for children aged 6–17 by the CWS caseworker at the initial family visit, which typically occurs 2–3 weeks prior to the initial CFT meeting. Based upon this initial visit and preliminary CANS results, informal and formal support persons are invited to the CFT meeting by the CFT Meeting Facilitation program. The CANS results are an integral component of the initial CFT meeting, during which the CWS caseworker guides discussion around the mental health needs that emerged from the initial CANS assessment and finalizes the Action Plan to attend to these needs. In addition to the above, those in the CFT + AAR will be guided through the AAR team effectiveness intervention, as facilitated by research staff, immediately following the CFT meeting. To optimize assessment of mental health services linkage, only CFTs which include a child with an identified mental health service determined by the preliminary administration of the CANS assessment by the CWS caseworker at the initial family visit will be included.

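### Under open allocation, the five CFTs per caseworker are picked by judgement and linkage is limited to children confirmed in the meeting; consecutive enrolment would reduce, not remove, the resulting selection bias

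*Protocol article*

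**What the plan says.** All references are to the protocol article.

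- **Allocation** (Specific aim 3): "The research team will utilize blocked randomization of CWS caseworker to intervention condition (CFT + AAR or CFT as usual) to ensure equal group sizes". Each of two regions has four caseworkers, two per arm. The same paragraph adds that "assignment of condition will be implemented by the research team without concealment or blinding".
- **Choice of caseworkers** (Participants): "The research team will partner with County CWS to identify appropriate and representative CWS caseworkers to follow over the course of 5 CFT meetings". The order of this step relative to allocation is not given.
- **Choice of meetings** (Participants): "The 5 CFT meetings per CWS caseworker will be identified to best represent County CWS open cases". The sentence is passive and gives no chooser, no timing, and no consecutive or random rule.
- **Eligibility of a CFT** (Participants): "only CFTs which include a child with an identified behavioral health services need will be included". Need comes from a preliminary CANS done by the caseworker at the first family visit. Specific aim 3 gives the same criterion.
- **Linkage population** (Participants): administrative data are extracted for children whose need is "identified via CANS screening and confirmed during initial CFT meeting". Under Specific aim 3, the caseworker leads the discussion of needs in that meeting, and the AAR takes place straight after it.
- **Design label** (Method, and the Methods part of the Abstract): "Using a parallel group trial design, with non-equivalent comparison groups".

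**The concern.** Randomising caseworkers balances the arms at caseworker level only. Families enter later, through their caseworker. If someone who knows the arm can choose among eligible families, or can influence which children count, the arms may differ in case mix for reasons unrelated to the AAR. This is the familiar identification bias of cluster-randomised trials.

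There are two routes here. The first is the choice of five CFTs under a rule that calls for judgement. The second is the narrowing of the linkage population by an event that occurs after allocation and is led by the randomised caseworker. Linkage is the last step of the article's mechanistic model, so the set of children in its denominator matters.

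The design label adds doubt. Non-equivalent groups is the usual term for a comparison without randomisation, which sits badly with a trial described as randomised.

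**Working it through.** **1. The plan's sampling frame.** Specific aim 3 gives 8 caseworkers with 5 CFTs each and about 8 members per CFT.
- CFTs: 8 × 5 = 40. Per arm: 4 × 5 = 20.
- Observations: 40 × 8 = 320. Both totals agree with the article.

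**2. What can be influenced once the arm is known.**

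| Step | Who acts | Arm known? |
|---|---|---|
| Caseworkers chosen | Research team with the County | Timing not stated |
| Preliminary CANS | Randomised caseworker | Yes, once allocated |
| Five CFTs chosen | Not stated | Not stated; allocation is open |
| Need confirmed in meeting | Discussion led by randomised caseworker | Yes |
| AAR (one arm) | Research staff, after the meeting | Yes |

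A child's need is confirmed before that child's own AAR. AAR exposure can therefore affect confirmation only through what the caseworker carries over from earlier CFTs. If the five CFTs run one after another, that excludes the first and leaves 4 of 5 per caseworker, or 4 × 4 = 16 of the 20 in the CFT + AAR arm.

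**3. Weight of one child.** Assuming one index child per CFT, 1/20 = 5 percentage points of an arm's linkage rate.

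**4. Three children (counts assumed).**
- Chosen differently: replacing three non-linkers by three linkers moves the arm by 3/20 = 15 points. This needs all three outcomes to flip.
- Dropped from the denominator: with 10/20 = 50.0% linked, removing three non-linkers gives 10/17 = 58.8%, a shift of 8.8 points. The extreme is 17/20 = 85% becoming 17/17 = 100%, a shift of 15 points.

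**5. Case-mix illustration (all inputs assumed, true effect zero).** Let likely linkers link at rate h and others at rate l, and let the share of likely linkers be s1 in one arm and s0 in the other. The spurious difference is (h − l)(s1 − s0).
- Mild: (0.70 − 0.40)(0.60 − 0.50) = 0.03.
- Strong: (0.80 − 0.30)(0.80 − 0.50) = 0.15.

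The range is 3 to 15 points.

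**6. Survey outcomes (illustration).** The article's effective sample size of 36 is reproduced by 320/[1 + (40 − 1)(0.20)] = 320/8.8 = 36.4, so about 18 per arm. The standard error of a standardised difference is √(2/18) = 0.333. A pure selection shift of b SD gives a two-sided rejection rate of Φ(b/0.333 − 1.96) + Φ(−b/0.333 − 1.96).

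| Assumed shift b | Rejection rate with no true effect |
|---|---|
| 0 | 5% |
| 0.2 | 9% |
| 0.3 | 15% |
| 0.5 | 32% |

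The article gives no figure from which h, l, s1, s0 or b could be estimated.

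**The case against.** The strongest reply is that this is a condensed article on a pilot test, and that sequence generation, order of enrolment and screening logs usually sit in the full protocol. That is right for those details, and their absence is not the point. The point rests on what the article does fix: open allocation, a judgement rule for meetings, and a linkage population defined by an event after allocation.

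It can also be said that CANS screening and in-meeting confirmation are usual service steps, and that the Discussion keeps caseworkers unaware of who consents. Both are true. But usual steps are still carried out by someone who knows the arm, and the consent safeguard covers neither the choice of CFTs nor the rating of need.

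Representativeness is a stated aim, and consecutive enrolment gives some of it up. This stands as a cost.

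Several stronger readings are tempting but not supported:
- *The research team and the County hand-pick families knowing the arm.* Their partnership is stated for choosing caseworkers; for meetings neither chooser nor timing is given. It is a possibility, not a fact.
- *The two definitions of need contradict each other.* They do not: one governs which CFTs enter, the other whose administrative data are extracted. The trouble is that the second is a subset formed after allocation.
- *The AAR changes whether a child's need is confirmed.* The order of events rules this out for the child's own AAR.
- *Allocations are predictable.* In a block of four allocated one at a time, on average 8/6 = 1.33 assignments are forced. The article does not describe one-at-a-time allocation, and the figure is irrelevant if caseworkers are all fixed first.

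**Conclusion.** The concern holds in limited form. The stated rules leave the comparison open to identification bias after randomisation, through discretionary choice of CFTs and through a linkage population conditioned on in-meeting confirmation. The CANS rating by the unblinded caseworker is a third route, which a better selection rule does not close. A reader might infer that consecutive enrolment would remove the bias; it removes only discretion among eligible CFTs.

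The size is unknown. The weight of 5 points per child rests on 40 separate CFTs, as Specific aim 3 states, and on one index child in each; the article requires only that a CFT include such a child. A shift of several points is plausible if a few children are chosen or dropped differently by arm; 15 points is an extreme. The false-positive rates above are illustrations under assumed shifts. The design label is a separate inconsistency: it is not evidence that allocation is other than random.

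**What to change.** 1. Identify all caseworkers of a region before any is allocated, then allocate them together.
2. Replace the judgement rule in Participants with the first five consecutive CFTs per caseworker that meet the preliminary-CANS criterion after a stated start date, and keep a log of skipped cases with reasons.
3. Analyse linkage in all children positive on the preliminary CANS, and report in-meeting confirmation descriptively by arm.
4. Reconcile the label of non-equivalent groups, in both the Abstract and Method, with the stated randomisation.
5. State as a limitation that the preliminary CANS is rated by a caseworker who knows the arm, so some bias can remain.

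The cost is protocol wording and a screening log. The 40 CFTs and 320 observations are unchanged. The one downside is that the case mix is whatever arrives rather than a chosen profile; describing it against County open cases would show how far it departs from them.

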### Measures

Several measures will be administered to participants to assess mechanisms and outcomes of the AAR. See Table 1 for a list of measures to be administered to intervention participants, and proposed mechanism and/or outcomes assessed by each measure.

#### Acceptability, feasibility, and appropriateness of intervention measure

This 9-item measure [51] will be administered to CFT + AAR participants immediately following completion of the CFT + AAR intervention to assess the extent to which the after-action review is appealing, liked, and welcomed in their setting (acceptability); fitting, suitable, and applicable in their setting (appropriateness); and possible and doable in their setting (feasible). Each of the 9 items is rated using the following response options: 1 = completely disagree, 2 = disagree, 3 = neither agree nor disagree, 4 = agree, and 5 = completely agree. Three subscales can be created by averaging responses for items representing acceptability, appropriateness, and feasibility, respectively.

#### Card-sorting task

Card sorting elicits individual mental models to understand how participants structure their knowledge. In open card sorts, participants are provided with a set of key concepts and asked to sort them into categories. Each participant then creates a label for each category. In closed card sorts, participants are similarly given a set of key concepts, but participants are given pre-defined categories that each concept must be sorted into. Within team environments, card sorting can be used to examine the degree to which team members are thinking about key concepts in a similar manner (e.g., team mental models) by comparing the categories and sorted content across members. Each participant will complete the card-sorting task immediately following completion of the intervention and will assess CFT team mental models by examining perceptions of member roles, responsibilities, and goals across CFT team members. In doing so, the concepts contained in the card sort will be representative of specific CFT roles, task responsibilities, and goals.

#### Collaboration & Satisfaction About Care Decisions (CSACD)

The 6-item collaboration subscale [57] assesses collaboration, shared responsibilities for planning, open communication, and coordination. The 3-item satisfaction subscale assesses satisfaction with the decision-making process, and satisfaction with the decision itself [57]. Although originally developed about care decisions for intensive care patients, it has since been used to measure collaboration and satisfaction with treatment planning plans associated with after-action reviews. Each participant will complete the CSACD immediately following their completion of the intervention. Participants respond on a 7-point Likert-type scale ranging from 1 = strongly disagree to 7 = strongly agree. Subscale scores are computed by calculating the average item response for items representing collaboration, and items representing satisfaction, respectively.

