**Discussion:**

By inclusion of child and family voice, the AAR-enhanced CFT should lead to increased fidelity to the CFT intervention and greater levels of parental satisfaction with the service and shared decision-making, thus resulting in enhanced follow-through with service plans and linkage to mental health treatment services for children. The knowledge gained by this randomized clinical trial has the potential to benefit service delivery and integration for CWS leaders, caseworkers, formal and informal CFT member support persons, parents/caregivers, and children with open cases. Improving intervention effectiveness, both at the system and family levels, is crucial for practice efficiencies and improved child and family outcomes.

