The AAR also aims to result in high-quality team processes exemplified by greater communication and coordination (Actions), and more positive perceptions of the specified goal and formulated strategy for the CWS child/family case (Transition). Group psychological safety and trust can influence “speaking up, or voice” [48], or verbal communication among team members. This open communication is vital for the CFT services intervention to reach its desired outcome—shared decision-making among team members, including CWS children/families, with regard to goals and the Action Plan. By targeting these proximal team effects, the AAR team-based implementation strategy aims to enhance CFT services intervention through the inclusion of child/family voice and shared decision-making. By increasing fidelity to the CFT services intervention, CWS child and family members may exhibit greater levels of satisfaction with the Action Plan, and specifically improved linkage to needed specialty behavioral health services.

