Immediately upon completion of each of the 5 CFT or CFT + AAR team meetings, the CWS caseworkers together with ~ 7 additional CFT members will provide data a via web-based online survey to assess mechanisms and outcomes. This results in 8 caseworkers leading 5 CFTs each for a total of 40 unique CFTs. Each of the 40 CFTs has ~8 participants, for a minimum total of 320 data points. See Fig. 2 for sampling.

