This project has the potential to benefit service delivery and integration for CWS leaders, caseworkers, formal and informal CFT member support persons, parents/caregivers, and children with open cases. By inclusion of child and family voice, the AAR-enhanced CFT should lead to increased fidelity to the CFT intervention and greater levels of parental satisfaction and shared decision-making, thus resulting in enhanced follow-through with service plans and linkage to mental health treatment services for children. Improving intervention effectiveness, both at the system and family levels, is crucial for practice efficiencies and improved child and family outcomes.

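### Greater satisfaction is expected among parents and families, but the satisfaction outcome is every member's own rating and neither planned test is tied to the parent's role

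*Protocol article*

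**What the plan says.** **Who is expected to be more satisfied.** The abstract's Discussion expects "greater levels of parental satisfaction with the service and shared decision-making". The closing Discussion expects "greater levels of parental satisfaction and shared decision-making". The section on the mechanistic model says that "CWS child and family members may exhibit greater levels of satisfaction with the Action Plan".

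**What is measured.** Table 1 lists one satisfaction outcome, the CSACD satisfaction subscale, under the construct of satisfaction with decisions. In the CSACD section, "The 3-item satisfaction subscale assesses satisfaction with the decision-making process, and satisfaction with the decision itself", and "Each participant will complete the CSACD immediately following their completion of the intervention". Scoring is per respondent: "Subscale scores are computed by calculating the average item response for items representing collaboration, and items representing satisfaction, respectively".

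**Who responds.** Under Specific aim 3, "the CWS caseworkers together with ~ 7 additional CFT members will provide data", and "Each of the 40 CFTs has ~8 participants, for a minimum total of 320 data points". The Participants section lists caseworkers, informal and formal meeting members, and parents/caregivers. It adds that children aged 6–17 will not be asked for study participation beyond usual services.

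**What is tested.** The Analytic plan tests a main effect of condition on implementation and child/family outcomes. It also includes a condition-by-participant interaction, to which it gives first importance; the within-meeting factor there is the individual team member. The Power analysis covers the condition main effect over all 320 observations.

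**The concern.** The expectation concerns parents and families, while the outcome covers everyone in the room. A caseworker's or clinician's CSACD score records that person's own satisfaction and is not a report on the parent's. Averaged over about eight members, the condition effect estimates team satisfaction. It could be positive with no change among parents, or close to zero when parents do gain.

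In the text, parental satisfaction is a step on the path from better meetings to follow-through and service linkage. If the pooled result is read as evidence for that step, the evidence is about a different group. For the child part of the mechanistic-model statement there are no satisfaction ratings at all.

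**Working it through.** **1. The plan's effective sample size.** Inputs from the Power analysis: n = 320, ρ = 0.20, n_eff = n/[1 + (n_clus − 1)ρ].
- n_clus = 40 (5 meetings × 8 members per caseworker): 320/(1 + 39 × 0.20) = 36.4. This reproduces the stated 36.
- n_clus = 8 (members per meeting, the level for which the text states ρ): 320/(1 + 7 × 0.20) = 133.3.

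Both clusterings are carried forward, because the formula and the verbal description of ρ point to different ones. The detectable f² of 0.10 is a separate matter and nothing below depends on it.

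**2. What the pooled effect can hide.** The number of parents/caregivers per meeting, k, is not given; k = 1 to 3 of 8 is assumed. The 0.5 SD gain is illustrative. The pooled effect is the respondent-weighted mean.

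| k | Gain of 0.5 SD in non-parents only: 0.5(8 − k)/8 | Gain of 0.5 SD in parents only: 0.5k/8 |
|---|---|---|
| 1 | 0.44 | 0.06 |
| 2 | 0.38 | 0.13 |
| 3 | 0.31 | 0.19 |

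**3. Whether the interaction closes the gap.** An interaction with individual member as the factor asks whether the condition effect varies between members. It does not say for whom. Variation that comes entirely from caseworkers or professionals would satisfy it. Even with a role factor, a significant interaction shows only that roles differ. A statement about parents needs the condition effect within the parent/caregiver role, and that contrast is not named.

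**4. Precision of a parent contrast.** With 40 meetings there are 40k parent ratings. ρ = 0.20 is carried over to parents as an assumption.

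| k | Parent ratings | By caseworker: 40k/[1 + (5k − 1)0.20] | By meeting: 40k/[1 + (k − 1)0.20] |
|---|---|---|---|
| 1 | 40 | 22.2 | 40.0 |
| 2 | 80 | 28.6 | 66.7 |
| 3 | 120 | 31.6 | 85.7 |
| All 8 members | 320 | 36.4 | 133.3 |

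Confidence intervals widen roughly with the square root of the ratio:
- by caseworker, from √(36.4/31.6) = 1.07 to √(36.4/22.2) = 1.28 times;
- by meeting, from √(133.3/85.7) = 1.25 to √(133.3/40.0) = 1.83 times.

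**The case against.** **The parental wording is expectation, not an endpoint.** This stands. The Discussion passages say what should follow and the mechanistic section says what may follow. Table 1 defines the construct without restricting it to parents, and Specific aim 3 sets no parental-satisfaction endpoint. A reader might infer that the trial commits itself to concluding on parents; the document does not support that. What remains is that the expectation is about parents and families and no named test addresses it.

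**The plan does look at differences between members.** This also stands in part. A reader might infer that only a pooled mean is tested, which would be wrong, since the interaction is given first importance. As step 3 shows, it does not identify parents.

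**Role coding could be in a fuller plan.** Possibly. The point does not rest on that silence, however. The article itself fixes an all-member outcome, an all-member powered test and an individual-level factor, alongside an expectation about parents.

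**Two further arguments should not be pressed.** The background section reports that most parents feel they have no voice, which may suggest that parents and professionals would respond differently. The same section reports that neither parents nor caseworkers see plans as mutually made, and it gives no data on diverging satisfaction. Nor is the unblinded caseworker a special reason for separation: nobody is blinded, and parents in the CFT + AAR arm take part in the review themselves.

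**A parent contrast is weaker in what is called a pilot test.** True, and the loss is not small if clustering is by meeting.

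**Conclusion.** The concern holds as a mismatch between the expected inference and the planned tests. A positive all-member main effect, or a significant condition-by-individual interaction, would not by itself support a statement about parental satisfaction, and a null main effect would not refute one.

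The documents do not show that parents and professionals will in fact diverge. The 0.44 to 0.31 SD figures show what the pooled test permits, not what is likely; they rest on the assumed 1 to 3 parents, an illustrative 0.5 SD, and a zero effect in one group. The mismatch itself does not depend on those assumptions. It is worth correcting before analysis, and the correction is cheap.

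**What to change.** In the Analytic plan, define the participant factor by role: parent/caregiver, caseworker, other formal or informal member. For CSACD satisfaction, prespecify the condition effect among parents/caregivers, estimated from that model, as the basis for any parental-satisfaction statement. Report the all-member main effect as team satisfaction.

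If the sponsor prefers to rely on the all-member test, reword the abstract, the mechanistic-model section and the closing Discussion to team-member satisfaction. Because children are not surveyed, the reference to child satisfaction needs rewording in either case.

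**Cost.** No new instrument is needed. Role on the team must be recorded with each survey, because the Demographics section lists working status/profession but not team role. The parent contrast has a wider interval, by the factors in step 4, and should be reported with its confidence interval.
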